**Secondary**	
• Assess safety **in pregnant women** randomized to receive the 2-dose Ebola vaccine regimen (Ad26.ZEBOV, MVA-BN-Filo group A) and in control women (unvaccinated pregnant women (group B))	• Frequency and relatedness of all SAEs in women from randomization until study end
• Assess safety **in neonates/infants born** to women randomized to receive the 2-dose Ebola vaccine regimen (Ad26.ZEBOV, MVA-BN-Filo (group A)) and in neonates/infants born to control women (unvaccinated pregnant women (group B))	• Frequency and relatedness of all SAEs in the newborns from birth until study end
• Assess the **reactogenicity** and unsolicited AEs of the 2-dose Ebola vaccine regimen (Ad26.ZEBOV, MVA-BN-Filo) in all vaccinated pregnant women (group A)	• Reactogenicity, defined as local and systemic solicited AEs occurring within 7 days after each dose, and unsolicited AEs within 28 days after each dose: ○ Frequency, grade, duration and causality for solicited systemic AEs and unsolicited AEs ○ Frequency, grade and duration for solicited local AEs
• Describe all pregnancy outcomes	• Pregnancy outcomes (example: normal delivery, Caesarian Section)
• Assess the **immunogenicity** of the 2-dose Ebola vaccine regimen (Ad26.ZEBOV, MVA-BN-Filo) in 150 pregnant women who are anticipated to receive both vaccine doses within the course of their pregnancy (a subset of the 1000 pregnant vaccinated women from group A) compared to 150 non-pregnant women vaccinated after delivery (a subset of group B)	• Anti-EBOV GP binding antibody concentrations, in ELISA units/mL (FANG ELISA) from: ○ Blood samples taken at pre-dose 1, 21 days post-dose 2, at delivery (group A subset only), and 1 year post-dose 1 ○ Cord blood if feasible from women in the group A subset
• Assess **persistence of maternal antibodies** in 75 infants born to women from the group A subset	• Anti-EBOV GP binding antibody concentrations, in ELISA units/mL (FANG ELISA) from a blood sample taken at 14 weeks of age

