## Interventions

### Explanation for the choice of comparators {6b}

The comparator group is unvaccinated pregnant women (group B). Robust data on background rates of adverse pregnancy outcomes are not available. Therefore, the unvaccinated pregnant women in group B (a non-interventional control) are important to establish the frequency and magnitude of changes in clinical endpoints that may occur in the absence of active vaccination during pregnancy (group A). Group B comparator women will receive the study vaccine after pregnancy termination.

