Humoral immunogenicity sample (serum)							•		•			
Cord blood sample									•		•	
Breast milk sample (*N* = 50)										•		

pre-dose;

pre- and post-dose

^a^Visits 7 and 11 for group A immunology subset participants only

^b^PP 1 refers to the day of pregnancy completion/termination. Visit 9 (PP 1) should occur on the day of pregnancy completion/termination or within 2 days

^c^Visit 10 (PP 43) scheduled to occur at routine 6 week post-partum visit. For women from group A not part of the immunogenicity subset, this visit will be the end of the trial

^d^Must be signed before first study-related activity

^e^Maternal demographic information to be collected at screening includes date of birth, race/ethnicity, education level, geographical location/residence, occupation, household size (number of persons living in the same home), and international travel history

^f^Information to be collected for medical and obstetric history, physical exams, and vital signs is specified in the protocol

^g^Urine dipstick for protein and glucose will be performed at these visits. If results 1 + or greater, then additional work-up for pre-eclampsia or gestational diabetes may be warranted

^h^Ultrasound not required at visit 2 if screening (visit 1) ultrasound completed within past 10 days and no other indication for ultrasound

^i^Investigator must check for acute illness or body temperature ≥ 38.0 °C at the time of vaccination. In such cases, the participant may be vaccinated at later time point

^j^Participants will be closely observed for a minimum of 30 min post-vaccination

^k^In all women of group A, solicited AEs (reactogenicity) and unsolicited AEs will be assessed 7 days post each dose and 28 post each dose respectively

^l^Includes any medical treatment/medications given to the mother during delivery (e.g., antibiotic prophylaxis)-specifying names of medications administered

^m^Information to be collected for delivery history and post-pregnancy examination is specified in the protocol

^n^Any routine laboratory assessment performed at time of delivery and other laboratory tests as medically indicated

^o^Not required if participant is not pregnant

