^p^In case pregnancy completion/termination in a group A pregnant woman occurs prior to receipt of dose 2, visits 9 and 10 should be performed: visit 10 being relative to visit 9 (2 day window). Visit 5 (dose 2 vaccination with a window of – 14 days, + 28 days) should in this case be performed after visit 9, with visits 6 and 8 being relative to actual dose 2 receipt (visit 5). All of these visits should be captured in RedCap cloud in addition to source documentation. Reactogenicity data (diary completion) should still be performed following dose 2 for group A women that have a pregnancy completion/termination prior to receipt of dose 2

**Table 3 Tab3:** Schedule of activities—women in group B

Visit #	1	2	3	4	5	6	7	8	9^a^	10^n^	11 ^a^	EE
**Visit timing**^**p**^		**Randomiz-ation (D1)**	**D1 + 28 days**	**D1 + 56 days**	**D1 + 12 weeks**	**Pregnancy completion/** **termination**	**Dose 1**	**Dose 2**	**Dose 2 + ** **21 days**	**Dose 2 + ** **28 days**	**Dose 1 + ** **365 days**	**Early** **exit**
**Visit day and window**	**-28 to 1**	**D1**	**D29 ± 7 days**	**D57** ** − 14 days, + 28 days**	**D85 ± 7 days**	**PP 1** ^b^ ** + 2 days**	**PP 43** ^c^ ** + 28 days**	**PP 99** **-14 days, + 28 days**	**PP 120** ** ± 14 days**	**PP 127** ** ± 3 days**	**Dose 1 + 365 ± 28 days**	
**Visit type**	Screening	**Random-ization**	Safety	Safety	Safety	Safety and immuno	**DOSE 1 group B**	**DOSE 2 group B**	Safety and immuno	Safety	Safety and immuno	Early exit
Assessment of understanding	•											
Written informed consent (ICF) ^d^	•											
Inclusion/exclusion criteria	•	•										
Demographics ^**e**^	•											
Medical and obstetric history ^f^ and prestudy meds	•											
Physical examination ^f^	•						•	•				•
Obstetric exam ^f^	•	•				•						•^o^
Targeted physical examination ^f^		•	•	•	•				•	•	•	
Vital signs ^f^ incl. body temperature	•	•	•	•	•	•			•	•	•	•
Urine pregnancy test ^g^	•											
Hematology, chemistry ^g^	•											
Urine dipstick/urinalysis ^g^	•	•	•	•	•							
Syphilis, HIV, hepatitis B and C, malaria screening ^g^	•											
Obstetric ultrasound ^h^	•	•^h^			•							•^o^
Biometric scan		•	•	•	•	•	•	•	•	•	•	•
Contact information	•	•	•	•	•	•	•	•	•	•	•	•
Randomization		•										
Pre-vaccination symptoms^i^												
Vaccination							•	•				
30 min post-vaccination observation ^j^							•	•				
Adverse maternal, fetal outcomes		•	•	•	•	•	•					
SAE recording		•	•	•	•	•	•	•	•	•	•	•

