Concomitant medications ^k^	•	•	•	•	•	•	•	•	•	•	•	•
Delivery history ^l^						•						
Post pregnancy physical examination ^l^						•						
Laboratory assessments ^m^						•						
Group B immunology subset supplemental procedures (*N* = 150)	**1**	**2**	**3**	**4**	**5**	**6**	**7**	**8**	**9**	**10**	**11**	EE
Humoral immunogenicity sample (serum)									•		•	
Breast milk sample (*N* = 10)												

pre-dose;

pre- and post-dose

^a^Visits 9 and 11 for group B immunology subset participants only

^b^PP1 refers to the day of pregnancy completion/termination. Visit 6 (PP1) should occur on the day of pregnancy completion/termination or within 2 days

^c^Visit 7 (PP 43) scheduled to occur at routine 6 week post-partum visit

^d^Must be signed before first study-related activity

^e^Maternal demographic information to be collected at screening includes: date of birth, race/ethnicity, education level, geographical location/residence, occupation, household size (number of persons living in the same home), and international travel history

^f^Information to be collected for medical and obstetric history, physical exams, and vital signs is specified in the protocol

^g^Urine dipstick for protein and glucose results will be performed at these visits. If results are 1 + or greater, then additional work-up for pre-eclampsia or gestational diabetes may be warranted

^h^Ultrasound not required at visit 2 if screening (visit 1) ultrasound completed within past 10 days and no other indication for ultrasound

^i^Investigator must check for acute illness or body temperature ≥ 38.0 °C at the time of vaccination. In such cases, the participant may be vaccinated at later time point

^j^Participants will be closely observed for a minimum of 30 min post-vaccination

^k^Includes any medical treatment/medications given to the mother during delivery (e.g., antibiotic prophylaxis)-specifying names of medications administered

^l^Information to be collected for delivery history and post-pregnancy examination is specified in the protocol

^m^Any routine laboratory assessment performed at time of delivery and other laboratory tests as medically indicated

^n^Visit 10: for women not part of the immunogenicity subset this visit will be the end of the trial

^o^Not required if participant is not pregnant

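### Maternal SAEs are counted to a study end that falls nominally 84 days later in group B, and that extra time follows group B's own vaccination

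*Protocol article*

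**What the plan says.** Under Outcomes {12}, Table 1 lists maternal safety as a secondary objective, assessed in group A and "in control women (unvaccinated pregnant women (group B". The endpoint is "Frequency and relatedness of all SAEs in women from randomization until study end", with the same words for both arms.

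Study end is set by the schedules under Participant timeline {13}:

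- Table 2, footnote c, group A: "Visit 10 (PP 43) scheduled to occur at routine 6 week post-partum visit", and "For women from group A not part of the immunogenicity subset, this visit will be the end of the trial". The printed window is ±14 days.
- Table 3, footnote n, group B: "Visit 10: for women not part of the immunogenicity subset this visit will be the end of the trial". In this table visit 10 is PP 127 ± 3 days.
- Both tables, immunogenicity subset (150 women per arm): the last visit is 365 days after dose 1. Dose 1 is at randomization in A and at PP 43 in B.

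Section {6b} states that "Group B comparator women will receive the study vaccine after pregnancy termination". Table 3 places dose 1 at PP 43 and dose 2 at PP 99, and marks SAE recording at both visits and at every later one.

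Statistical methods {20a} puts all safety analyses on the full analysis set of randomized women and plans no formal testing. For SAEs it mentions neither a cut-off at group B's first dose nor person-time. By contrast, the primary maternal endpoint in Table 1 stops at a common point, six weeks after the pregnancy ends.

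**The concern.** The percentage of women with at least one SAE can only rise with longer observation. If both arms are followed to their own study end, group B accumulates more women with an SAE even when the vaccine does nothing. Any SAE caused by group B's own doses would also be counted in the control column, although the objective calls that group unvaccinated. Both effects make group A look better by comparison.

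This matters for three reasons. Group B exists, according to section {6b}, because robust background rates are lacking. Solicited and unsolicited AEs are not collected in group B, so SAEs are the only general adverse event data available in both arms. And the Objectives section says the study is meant to support a label change on use in pregnancy.

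**Working it through.** The plan gives no figure for this endpoint to reproduce. Its sample-size figures (63% and 0.3%) do reproduce, but they do not bear on this point.

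**1. Gap outside the subset (about 850 of 1000 women per arm).**

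- Nominal: 127 − 43 = 84 days.
- Over the printed visit windows: from (127 − 3) − (43 + 14) = 67 to (127 + 3) − (43 − 14) = 101 days.
- If group B's visit 10 moves with the dose 2 window (−14, +28): from (99 − 14 + 28 − 3) − 57 = 53 to (99 + 28 + 28 + 3) − 29 = 129 days.

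On the nominal schedule all 84 days are on or after group B's dose 1.

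**2. Observation time.** Let T be days from randomization to the end of pregnancy. The article does not give T, so a range is shown. Follow-up is T + 42 in A and T + 126 in B. The share of B's follow-up after its own dose 1 is 84/(T + 126).

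| T | A (days) | B (days) | B/A | Share of B after its dose 1 |
|---|---|---|---|---|
| 56 | 98 | 182 | 1.86 | 46% |
| 84 | 126 | 210 | 1.67 | 40% |
| 140 | 182 | 266 | 1.46 | 32% |
| 196 | 238 | 322 | 1.35 | 26% |

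**3. Subset.** A is followed 365 days and B is followed T + 42 + 365 = T + 407 days. The gap is T + 42 days: 126 at T = 84 and 182 at T = 140.

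**4. Illustration with no vaccine effect.** Take a risk r in A up to PP 43, and a hazard after PP 43 equal to k times the earlier hazard. For women outside the subset:

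risk in B = 1 − (1 − r)^[1 + 84k/(T + 42)]

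Here r = 2.8%, the SAE proportion in vaccinated adults in the earlier non-pregnant trials (section on clinical efficacy/safety studies). It is an assumption for this population, and so is k.

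- T = 140, k = 0.1: 1 − 0.972^1.046 = 2.9%, or 1.3 extra women per 1000 in B.
- T = 140, k = 1.0: 1 − 0.972^1.462 = 4.1%, or 12.7 extra per 1000.
- T = 84, k = 0.1 and 1.0: 3.0% and 4.6%.

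At T = 140 the apparent A/B risk ratio is 0.96 to 0.69 when the true ratio is 1.

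**5. Common cut-off.** If both arms stop at PP 43, before group B's dose 1, the nominal gap is 43 − 43 = 0 days and group B contributes only unvaccinated time.

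**6. Two related schedule points.**

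- The six-week visit is PP 43 ± 14 in A (PP 29 to PP 57) but PP 43 + 28 in B (PP 43 to PP 71). In each table it is the last visit at which adverse maternal outcomes are marked.
- For group A women whose pregnancy ends before dose 2, Table 2 footnote p places dose 2 after the pregnancy visit, "with visits 6 and 8 being relative to actual dose 2 receipt (visit 5"). Nominally visit 8 is day 85 and PP 43 is day T + 43, so visit 8 comes after visit 10 whenever T is below 42. Footnote c nevertheless calls visit 10 the end of the trial. For these women the gap to group B narrows to T + 42 days if they are followed to visit 8.

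**The case against.** The endpoint is secondary and descriptive. Table 1 speaks of assessing safety in A and in controls, and uses explicit comparison wording only for immunogenicity. The statistical section attaches its tabulation by group to the primary outcomes and specifies no cumulative SAE contrast. Recording SAEs through group B's vaccination is sound practice. A split into periods before and after vaccination is common content for a statistical analysis plan, which is not shown and to which detailed methods are deferred. The endpoint also includes relatedness, and the immunogenicity objective recognises that group B women are vaccinated after delivery.

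Much of this stands. No test is planned, so no error rate is affected, and the analysis plan may already set a cut-off. It does not remove the point. Table 1 fixes the end of the window in identical words for two arms whose study ends differ, and labels the comparator unvaccinated for a window that includes its vaccination. Naming group B as the control invites a side-by-side reading of the percentages. The primary maternal endpoint shows that a common window was available.

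A reader might go further and infer that the primary endpoints or the infant data share the problem. They do not share this unequal end. The primary maternal window is defined to a common point, and infant follow-up ends at PP 99 in every group (Table 5), so there is no case for splitting infant data at the mother's dose 1.

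A reader might also infer that group A's six-week window is systematically cut short. PP 57 is as permissible as PP 29, the visit is tied to routine six-week care, and outcomes may be abstracted from medical records. The documents show unequal windows, not a demonstrated loss of events.

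**Conclusion.** The point holds as a defect in how the secondary maternal SAE endpoint is fixed, and it should be corrected. The 84 nominal days, their timing after group B's own doses, and the T + 42 day gap in the subset follow directly from the schedules. The direction of the effect on a crude percentage is also clear: it favours the vaccine.

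The size is not known. The extra time begins after six weeks post-partum, when pregnancy-related SAEs should be fewer, so the excess may be small. The 2.9% to 4.1% range rests on three assumptions: 2.8% in A, T = 140, and a later hazard between 0.1 and 1.0 times the earlier one. A large bias could be inferred by assuming a constant hazard and a higher SAE risk, but the documents supply neither.

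**What to change.** Define the A-versus-B maternal SAE comparison as running from randomization to six weeks after the pregnancy ends and before group B's dose 1. This is the window of the primary maternal endpoint, with the added condition on dose 1. Tabulate later SAEs separately, and label group B's SAEs after its dose 1 as post-partum vaccinee data. Keep recording SAEs to study end as planned.

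SAEs are already recorded throughout, so this is a wording change to Table 1 and the analysis plan. The small cost is that later SAEs leave the between-arm contrast.

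Separately, the sponsor should reconcile two sets of passages: the differing windows for the six-week visit (Table 2 visit 10, Table 3 visit 7), and the end of trial for group A women whose pregnancy ends before dose 2 (Table 2 footnotes c and p).

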### Intervention description {11a}

The Ebola vaccine regimen in this trial is comprised of two vaccines:Ad26.ZEBOV is a replication-incompetent monovalent vaccine encoding the full-length glycoprotein (GP) from Ebola virus (EBOV) Mayinga. A 0.5-mL injection into the deltoid muscle in the upper arm (or thigh if needed) of 5 × 10^10^ vp will be administered at day 1 (enrollment).MVA-mBN226B, further referred to as Modified Vaccinia Ankara (MVA)-BN®-Filo, does not replicate in human cells and is a multivalent vaccine encoding the EBOV GP, the Sudan virus (SUDV) GP, the Marburg virus (MARV) Musoke GP, and the Taï Forest virus (TAFV, formerly known as Côte d’Ivoire ebolavirus) nucleoprotein (NP). A 0.5 mL injection into the deltoid muscle in the upper arm (or thigh if needed) of 1 × 10^8^ InfU will be administered at day 57 (− 14 days + 28 days) after the Ad26.ZEBOV dose.

The second dose of vaccine should ideally be given in the opposite arm/thigh (unless the opposite arm/thigh has a condition that prevents evaluation of the arm/thigh after injection). The Ad26.ZEBOV and MVA-BN-Filo vaccines will be manufactured and provided under the responsibility of Janssen Vaccines and Prevention B.V.

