### Participant timeline {13}

See Tables 2, 3, 4, and 5 for the participant schedule of activities and visit timeline.

**Table 2 Tab2:** Schedule of activities—women in group A

Visit #	1	2	3	4	5	6	7 ^a^	8	9	10	11^a^	EE
**Visit timing**^**p**^		**Dose 1**	**Dose 1** ** + 7 days**	**Dose 1 + ** **28 days**	**Dose 2**	**Dose 2 + ** **7 days**	**Dose 2 + ** **21 days**	**Dose 2 + ** **28 days**	**Pregnancy completion/** **termination**	**PP 1 + 42**	**Dose 1 + ** **365 days**	**Early** **Exit**
**Visit day and window**	** − 28 to 1**	**D1**	**D8 ± 3 days**	**D29 ± 7 days**	**D57** ** − 14 days, + 28 days**	**D64 ± 3 days**	**D78 ± 3 days**	**D85 ± 7 days**	**PP 1** ^b^ ** + 2 days**	**PP 43** ^c^ ** ± 14 days**	**Dose 1 + 365 ± 28 days**	
**Visit type**	Screening	**DOSE 1 group A**	Safety	Safety	**DOSE 2 group A**	Safety	Immuno	Safety	Safety and immuno	Safety	Safety and immuno	Early exit
Assessment of understanding	•											
Written informed consent (ICF) ^d^	•											
Inclusion/exclusion criteria	•	•										
Demographics ^**e**^	•											
Medical and obstetric history ^f^; pre-pregnancy and pre-study meds	•											
Physical examination ^f^	•				•					•		•
Obstetric exam ^f^	•	•			•				•			•^o^
Targeted physical exam ^f^		•	•	•		•	•	•			•	
Vital signs ^f^ incl. body temperature	•		•	•		•	•	•	•	•	•	•
Urine pregnancy test ^g^	•											
Hematology, chemistry ^g^	•											
Urine dipstick/urinalysis ^g^	•	•		•	•			•				
Syphilis, HIV, hepatitis B and C, malaria screening^g^	•											
Obstetric ultrasound ^h^	•	•^h^						•				•^o^
Biometric scan	•	•	•	•	•	•	•	•	•	•	•	•
Contact information	•	•	•	•	•	•	•	•	•	•	•	•
Randomization		•										
Pre-vaccination symptoms ^i^												
Vaccination		•			•							
30 min post-vaccination observation ^j^		•			•							
Solicited AE collection ^k^		•	•		•	•						
Unsolicited AE collection ^k^		•	•	•	•	•	•	•				
Distribution of participant diary, rulers and thermometers ^k^		•			•							
Participant diary review by site staff			•			•						
Adverse maternal, fetal outcomes		•	•	•	•	•	•	•	•	•		
SAE recording		•	•	•	•	•	•	•	•	•	•	•
Concomitant medications ^l^	•	•	•	•	•	•	•	•	•	•	•	•
Delivery history ^m^									•			
Post pregnancy physical examination ^m^									•			
Laboratory assessments^n^									•			
Acceptability questionnaire									•	•		•
Group A immunology subset supplemental procedures (*N* = 150)	**1**	**2**	**3**	**4**	**5**	**6**	**7**	**8**	**9**	**10**	**11**	

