## Statistical methods

### Statistical methods for primary and secondary outcomes {20a}

For purposes of analysis, the following populations are defined:Full analysis set (FAS): The FAS will include all randomized participants. All safety analyses will be made on the FASPer-protocol immunogenicity (PPI): The PPI population will include all randomized and vaccinated participants for whom immunogenicity data are available excluding participants with major protocol deviations expecting to impact the immunogenicity outcomes

Of note, women enrolled from Umurinzi will be analyzed separately. No formal statistical testing is planned. The number and percentage of participants screened, enrolled, randomized, receiving two vaccine doses, and completing follow-up will be summarized by study arm.

Baseline demographic characteristics (including gestational age and obstetric risk assessment) will be tabulated overall and by study arm.

The frequency and percentage of women for whom at least one of the indicated adverse outcomes was reported as a primary endpoint (see above) will be summarized by study group. For each separate adverse maternal/fetal and adverse neonatal/infant outcome, the number and percentage of participants who experience at least 1 occurrence of the given event will also be tabulated by study group (groups A and B, and their infants). The verbatim terms used in the CRF by investigators to identify AEs will be coded using the Medical Dictionary for Regulatory Activities (MedDRA). The reporting of the categorical safety data will include the incidence, severity, relatedness, and type of AEs. Continuous safety parameters will be analyzed descriptively (showing the mean, standard deviation, median, and quartiles [Q1 and Q3]).

For participants from group A, all reported AEs, events-related diary information (solicited local at injection site and systemic, and unsolicited) with onset within 4 weeks post dose 1 or dose 2 vaccination (i.e., treatment-emergent AEs) will be included in the analysis. For each AE, the number and percentage of participants who experience at least 1 occurrence of the given event will be summarized. Of note, solicited and unsolicited AEs will not be collected for group B participants.

Summaries, listings, datasets, or participant narratives may be provided, as appropriate, for those participants who die, who discontinue intervention due to an AE, or who experience a severe or a serious AE.

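### Visits 3, 6 and 8 may fall before the 7-day solicited and dose 2 28-day unsolicited AE periods end; for unsolicited AEs after dose 2, no later collection is scheduled

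*Protocol article*

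**What the plan says.** The secondary reactogenicity endpoint in Table 1 covers "local and systemic solicited AEs occurring within 7 days after each dose, and unsolicited AEs within 28 days after each dose". Duration is a named measure: the table lists "Frequency, grade, duration and causality for solicited systemic AEs and unsolicited AEs", and also frequency, grade and duration for solicited local AEs. The statistical methods section {20a} includes group A events "with onset within 4 weeks post dose 1 or dose 2 vaccination".

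Table 2 sets the group A visits that serve these periods:

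- Visit 3 (dose 1 + 7) at D8 ± 3 days and visit 6 (dose 2 + 7) at D64 ± 3 days.
- Visit 4 (dose 1 + 28) at D29 ± 7 days and visit 8 (dose 2 + 28) at D85 ± 7 days.
- The row "Solicited AE collection" is marked at visits 2, 3, 5 and 6.
- The row "Participant diary review by site staff" is marked at visits 3 and 6 only.
- The row "Unsolicited AE collection" is marked at visits 2 to 8 and at none after that.

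Footnote k to Table 2 says that "solicited AEs (reactogenicity) and unsolicited AEs will be assessed 7 days post each dose and 28 post each dose respectively". It gives no rule for a visit held early but within its window.

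**The concern.** A visit can comply fully with Table 2 and still come before the period it is meant to close has ended. If nothing later collects the same data, the endpoint for that woman covers less than its stated period. Events starting in the missing days would not be counted, and an event still ongoing at the last collection visit could have its duration cut short.

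Any such error runs in one direction, towards understatement. Group B has no solicited or unsolicited AE collection, so no control arm shares or offsets it. The trial is intended to support relaxing label restrictions on use in pregnancy, so the reactogenicity and AE tables should cover the periods they name.

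**Working it through.** **Inputs.** Periods of 7 and 28 days (Table 1); dose 1 on D1 and dose 2 nominally on D57; visit windows and collection marks (Table 2). Visits 6 and 8 are counted from the actual dose 2. The visit-timing row of Table 2 labels them that way, and footnote p states it for women whose pregnancy ends before dose 2.

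**Nominal days.** Dose day + period: 1 + 7 = D8, 1 + 28 = D29, 57 + 7 = D64, 57 + 28 = D85. All four match Table 2.

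**Earliest permitted visit and days still to come.** Earliest visit = nominal day − window. Days still to come = period − (earliest visit − dose day).

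| Visit | Earliest day | Days after dose | Days still to come |
|---|---|---|---|
| 3 | 8 − 3 = D5 | 4 | 7 − 4 = 3 of 7 (43%) |
| 6 | 64 − 3 = D61 | 4 | 7 − 4 = 3 of 7 (43%) |
| 4 | 29 − 7 = D22 | 21 | 28 − 21 = 7 of 28 (25%) |
| 8 | 85 − 7 = D78 | 21 | 28 − 21 = 7 of 28 (25%) |

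**Does a later scheduled visit recover those days?**

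- *Unsolicited, after dose 1: yes.* The second vaccine "will be administered at day 57 (− 14 days + 28 days) after the Ad26.ZEBOV dose", so visit 5 is no earlier than 57 − 14 = D43, or dose 1 + 42 days. That is after the 28-day period has ended, and unsolicited collection is marked there. Women who never attend visit 5 are the exception.
- *Unsolicited, after dose 2: no.* Visit 8 carries the last mark. Visit 7 (D78 ± 3) is for the immunology subset only and falls at dose 2 + 24 days at the latest, so it does not reach day 28 either. SAE recording continues at every later visit and adverse maternal/fetal outcomes are recorded through visit 10, so what can be lost is non-serious AEs with onset on days 22 to 28.
- *Solicited, both doses: only in part.* Visits 3 and 6 carry the last solicited mark and the only diary review for their dose. Days 5 to 7 also lie inside the 28-day unsolicited period, so visits 4 and 8 may pick up a symptom from those days. It would then probably be entered as an unsolicited AE, and section {20a} tabulates those separately from solicited AEs.

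**Average loss, as an illustration.** The article gives no distribution of visit timing. Assume, only to show scale, that visits are spread evenly over the days of each window:

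- Visits 3 and 6: 3/7 = 43% of women seen early; mean shortfall (1 + 2 + 3)/7 = 0.86 day, which is 12% of 7 days.
- Visit 8: 7/15 = 47% seen early; mean shortfall (1 + 2 + … + 7)/15 = 28/15 = 1.87 days, which is 6.7% of 28 days.

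If sites schedule close to the nominal day, the loss is smaller than this.

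**The case against.** The strongest reply is that early review does not mean lost data. The article nowhere says that the diary is taken back at review, that entries stop there, or that duration is cut at the visit. Footnote k states the full periods, the harms section {22} requires all AEs to be recorded, and section {20a} includes all reported events with onset within 4 weeks. Diary retention and telephone completion are details that an article normally leaves to the full protocol. This stands as a limit on the solicited part: days 5 to 7 may go unreviewed, but they cannot be called unobserved.

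It does not remove the dose 2 gap. There the article is not silent: Table 2 stops the unsolicited row at visit 8, while other rows continue, and allows that visit a week before the period ends.

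A reader might infer three stronger things, none of which the article supports:

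- That unsolicited AEs are cut short after both doses. Visit 5 collects them again well after day 28 of dose 1.
- That unreviewed days are analysed as event-free. This is a plausible consequence of tabulating participants with at least one event and imputing nothing, but no rule says so.
- That dose 2 will look better tolerated than dose 1. No comparison between doses is planned.

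It is also fair that these are descriptive secondary endpoints in group A, with no formal testing, and that 43% and 25% describe only a woman at the extreme edge of the window.

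**Conclusion.** The windows and the endpoint periods do not fit together at visits 3, 6 and 8. The firm part is non-serious unsolicited AEs on days 22 to 28 after dose 2: up to 7 of 28 days per woman, with no later scheduled collection. The softer part is solicited AEs: up to 3 of 7 days per dose may go without diary review, with possible truncation of durations.

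The effect on solicited incidence is probably small, on the assumption that most reactions begin in the first days after a dose; the article gives no onset data. Duration and late unsolicited events after dose 2 are more exposed. The total effect scales with the number of women seen early, which is unknown.

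The conclusion rests on visits 6 and 8 being counted from the actual dose 2, and on the full protocol, which is not shown, containing no instruction to complete the period after an early visit. The primary maternal, fetal and infant outcomes and SAEs are not affected. This is a modest point about data capture that is worth correcting.

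**What to change.** Either of two changes closes the gap:

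1. Make the assessment windows one-sided: visits 3 and 6 at dose + 7 days (0/+3), and visit 8 at dose 2 + 28 days (0/+7), with visits 6 and 8 counted from the actual dose 2.
2. Keep the windows. For women seen early, continue the diary through dose + 7 days and make a telephone contact at or after dose 2 + 28 days for unsolicited AEs. State this in footnote k.

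Either brings the shortfall at visits 3, 6 and 8 to 0 days when followed. Adding an unsolicited AE mark at visit 9 would not be enough: where pregnancy ends before dose 2, footnote p places visit 9 before that dose.

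Recruitment was expected to finish around January 2022, so many women may already have passed these visits. For them, report by dose the number whose solicited or unsolicited period was incomplete, next to the frequency and duration tables.

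The cost is slightly narrower scheduling windows or one telephone contact per woman seen early at visit 8. The article already describes telephone and message contact with participants. Vaccination timing does not change.
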